## Methods

### Participants

#### Inclusion/Exclusion Criteria

The clinical sample for this study will comprise participants who meet the following inclusion criteria: (1) 40–60 years of age, who are either single or have a partner; (2) peri-menopausal and have had a menstrual period within the previous 12 months as per the STRAW definition (21), (3) cut-off score of 26 or lower on the Female Sexual Functioning Index, indicating sexual dysfunction (22), (4) medication stable (e.g., HT), with no changes in dosing for the previous 3 months (19), (5) no psychological treatment to address sexual dysfunction and/or sexual concerns within the previous 6 months; and (6) speak, read, and write in English to comprehend testing procedures and written materials in treatment. Participants will be excluded if: (1) they have any psychotic disorders, or current substance and/or alcohol dependence; and/or (2) are severely depressed/suicidal at time of the intake assessment as they would not be able to meaningfully participant in treatment.

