#### Sample Size

Based on our data from our CBT for menopausal symptoms randomized controlled trial (19), as well as in previous studies (20) assessing the efficacy of CBT for sexual concerns in menopausal women, we estimate a medium effect size of 0.5 for our study. Using an ANCOVA power analysis to calculate sample size, and with a level of significance set at α = 0.05 and a study power set at 80%, 68 participants are required to conduct our study. Adjusting our sample for a 20% attrition rate, we plan on recruiting 82 participants.

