#### Study Design

This is an open waitlist study whereby eligible participants will be assigned to a treating clinician and will complete 4 weeks of the CBT-SC-Peri treatment protocol, followed by a post-treatment assessment. If a treating clinician is not immediately available, participants will be placed on that clinician's waitlist for 4 weeks. They will then be re-assessed after the 4-week waitlist period and then undergo the four-session treatment, followed by a post-treatment assessment. For a flowchart of trial procedures, see Figure 1.

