### Study Measures

The assessment battery includes various measures of sexual concerns, vasomotor symptoms, mood, anxiety, relationship, health, body image, cognitive flexibility, and treatment satisfaction. The primary outcome of this trial, sexual satisfaction, is assessed with the Female Sexual Desire Questionnaire. Please see Table 1 for a list of measures and their associated timing.

**Table 1 T1:** Timing of measurements.

**Procedures and Measures**	**CBT-SC-PERI**		**Waitlist** **+** **CBT-SC-PERI**		
	**Baseline**	**Post-treatment**	**Baseline**	**Post-waitlist**	**Post-treatment**

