### Primary Outcome

#### The Female Sexual Function Index

The Female Sexual Function Index (FSFI) (23) is a six-domain measure of female sexual functioning including sexual desire, subjective arousal, lubrication, orgasm, satisfaction, and pain. The FSFI has demonstrated excellent internal consistency (α = 0.82–0.96) and test-retest reliability when used in menopausal women (22–24). A clinical cut-off score of 26 or lower has been suggested to identify significant sexual dysfunction (22). The FSFI is considered as a gold-standard in assessing sexual functioning in women (25).

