### Statistical Analysis Plan

Treatment response will be determined using multiple measures, as identified in the assessment battery, and distinguished between primary and secondary efficacy analyses. A series of repeated measures analysis of covariance (ANCOVA) will be used to examine condition differences. A two (treatment vs. wait-list) by two (time: pre-treatment, post-treatment) repeated measures ANCOVA will be used to examine differences in both primary and secondary outcomes, specifically sexual satisfaction and desire, body image, partner satisfaction, vasomotor symptoms, as well as depression and anxiety symptoms. Covariates for all analyses will include age, current marital status, medication use at baseline, treatment delivery method, and baseline depression and anxiety severity. If continuous variables do not meet the assumptions of normality, as assessed by the Shapiro-Wilk test, we will use non-parametric methods, with alpha levels set at 0.05.

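### A Shapiro-Wilk test on the variables, not the residuals, decides whether the adjusted model is replaced by unnamed non-parametric methods, and nothing secures the covariates if it is

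*Protocol article*

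**What the plan says.** The Statistical Analysis Plan section of the protocol article names one model for primary and secondary outcomes: "A two (treatment vs. wait-list) by two (time: pre-treatment, post-treatment) repeated measures ANCOVA will be used". It then lists the adjustment set: "Covariates for all analyses will include age, current marital status, medication use at baseline, treatment delivery method, and baseline depression and anxiety severity". The next sentence is the rule at issue: "If continuous variables do not meet the assumptions of normality, as assessed by the Shapiro-Wilk test, we will use non-parametric methods". It keeps alpha at 0.05. It names no replacement method and does not mention residuals.

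Three other places bear on it:

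- **Entry.** The Inclusion/Exclusion Criteria require a "cut-off score of 26 or lower on the Female Sexual Functioning Index, indicating sexual dysfunction".
- **Primary instrument.** Table 1 and the Primary Outcome section give the FSFI, described as follows: "The Female Sexual Function Index (FSFI) (23) is a six-domain measure of female sexual functioning". The Study Measures text says otherwise: "The primary outcome of this trial, sexual satisfaction, is assessed with the Female Sexual Desire Questionnaire".
- **Allocation.** The Study Design section says: "If a treating clinician is not immediately available, participants will be placed on that clinician's waitlist for 4 weeks". Groups are therefore formed by clinician availability, not by randomisation.

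**The concern.** The normality assumption behind ANCOVA concerns what is left after group, time and covariates are fitted. The raw variables may be far from normal while the model is sound, so a rule aimed at them can reject a valid analysis.

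This trial can provoke that error. An upper limit at entry cuts off the right tail of baseline FSFI. In a two-by-two repeated measures model the pre-treatment score is one level of the dependent variable, so a literal reader of the rule would test it.

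The consequence matters more than usual because the comparison is not randomised. The listed covariates are the only stated control for differences between women treated at once and women who wait. The commonly used rank tests (Mann-Whitney, Wilcoxon) take no covariates. If they are what the rule means, a test that says nothing about model validity could remove that control. The rule also chooses the method from the trial's own data.

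**Working it through.** The plan attaches no figure to this rule, so there is none to reproduce. The checks are simulations with 3,000–4,000 runs per setting for the main figures and two-sided alpha of 0.05.

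**Inputs from the article.** N = 68 analysed and an effect stated as "we estimate a medium effect size of 0.5 for our study" (Sample Size section); FSFI of 26 or lower at entry.

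**Assumptions, because the article gives no figure.**
- An equal split, 34 per group.
- A normal FSFI score in the source population, cut at the mean plus c SD. No FSFI mean or SD is given, so c is varied.
- A baseline-to-outcome correlation of 0.6 in step 1.
- A covariate-to-outcome correlation r of 0.5 to 0.68 in step 2. The upper value is the correlation at which d = 0.5 leads to 68: 126 × (1 − 0.68²) = 67.7.

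**Step 1. What does the test reject?** Baseline x is normal, truncated above at c. The post score is y = 0.6x + e with normal e. Shapiro-Wilk is applied at N = 68.

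| Cut at mean + c SD | Share at or below cut | Baseline rejected |
|---|---|---|
| 0 | 50% | 99% |
| 0.5 | 69% | 93% |
| 1.0 | 84% | 67–69% |
| 1.5 | 93% | 26–28% |
| 2.0 | 98% | 8% |
| 2.5 | 99% | 4–5% |

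Ranges show the spread between repeated simulations. Over the cuts from 0 to 1.5 SD:
- post-treatment scores are rejected in about 5–6%;
- residuals of a baseline-adjusted model are rejected in about 4–5%;
- residuals of change scores, which is what the condition-by-time test uses with two time points, are rejected in about 4–6% (r from 0.5 to 0.7);
- the type I error of the baseline-adjusted ANCOVA stays at about 5%.

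Near-nominal rejection of the baseline-adjusted residuals follows from the normal e. The point is that truncation of x does not by itself damage them. With clearly skewed residuals (gamma, shape 2) and a truncated baseline, ANCOVA type I error was still 4.7%.

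**Step 2. What is lost if the fallback is unadjusted?** There is no true effect. One prognostic covariate differs between groups by b SD, so the unadjusted outcome shifts by r × b SD. For a Mann-Whitney test the approximate noncentrality is

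λ = r × b × √(34/2) × √(3/π), and type I error ≈ Φ(λ − 1.96) + Φ(−λ − 1.96).

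| b | r | Shift r × b | λ | Formula | Simulated, unadjusted | Simulated, adjusted |
|---|---|---|---|---|---|---|
| 0.3 | 0.50 | 0.150 | 0.60 | 9% | 9% | 4–5% |
| 0.3 | 0.68 | 0.204 | 0.82 | 13% | 12% | 5% |
| 0.5 | 0.50 | 0.250 | 1.01 | 17% | 16% | 5% |
| 0.5 | 0.68 | 0.340 | 1.37 | 28% | 27% | 5% |

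Allowing for simulation error, this is about 8–13% at 0.3 SD and 16–27% at 0.5 SD, against about 5% with adjustment.

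**The case against.** Three stronger readings are tempting. None is supported.

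**That failure is likely for the primary outcome.** Only the baseline FSFI total is capped; post-treatment scores fail at about the nominal rate. The baseline rate depends on where 26 falls in an FSFI distribution that the article does not give. At +1.5 SD it is already only about 27%, at +2 SD about 8%, and with 34 women tested in one group at +1.5 SD about 13%. The article also contradicts itself on the primary instrument. If it is the FSDQ, or only the satisfaction domain of the FSFI, the cut-off does not truncate it directly. What stands is that the cut-off can trigger the switch.

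**That the switch does discard every covariate.** The sentence just before the rule speaks of covariates for all analyses, which may be meant to include the fallback. Rank-based ANCOVA exists, and an article may leave the exact method to a fuller plan. What stands is that nothing in the text secures adjustment, and the best-known rank tests cannot carry it.

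**That the switch costs a large amount of power.** Setting a Mann-Whitney test of post scores (about 49–51% at d = 0.5) against a baseline-adjusted ANCOVA (64–80%) is not like for like, because the planned condition-by-time test is a comparison of change. At 34 per group and r of 0.5 to 0.7, a t test on change has about 53–75% power and Mann-Whitney on change about 50–72%. The rank step alone costs roughly 3 points. Power is therefore not the ground for this point.

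None of this answers the central fault, which is that the rule tests variables where the assumption concerns residuals. That is stated in the article, not left to another document.

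**Conclusion.** The point holds in a limited form. The rule is wrong as written whichever instrument is primary, because its trigger is not evidence about the model it replaces. If the FSFI total is primary, the entry criterion can set it off at baseline in about 27–99% of trials at N = 68. This assumes an underlying normal score cut between its mean and +1.5 SD, and the risk largely disappears by +2 SD. Residuals in the same simulations are unremarkable.

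The harm is conditional. It arises if the fallback is unadjusted and a measured prognostic covariate differs between groups. Type I error is then about 8–13% at a 0.3 SD difference and 16–27% at 0.5 SD, against about 5% with adjustment. The size of any imbalance and the correlations are assumptions. Adjustment also protects only against the covariates that are listed.

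This should be corrected before the data are analysed. It does not show that the planned adjusted model is unsound.

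**What to change.** Replace the Shapiro-Wilk sentence with a rule along these lines:

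- The covariate-adjusted model is the primary analysis for every continuous outcome, whatever a normality test on any variable shows.
- Normality is judged on model residuals, by plots.
- Where residuals are clearly non-normal, robust (for example HC3) or bootstrap 95% confidence intervals are reported, with a rank-based ANCOVA using the same covariates as a sensitivity analysis.

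Other packages would also do, provided that they judge residuals and keep the covariates. The primary instrument should be reconciled between Study Measures and Table 1, so that it is clear whether the cut-off acts on the primary outcome.

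The cost is one sentence and slightly more analysis work. If HC3 is used, simulated power falls by about 1–2 points (0.71 to 0.69 with normal residuals, 0.71 to 0.70 with skewed ones).

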### Dissemination

Study results will be disseminated through peer-reviewed scientific publications, as well as relevant national and international conferences (e.g., World Congress on Women's Mental Health). Further dissemination in the form of media outlets (e.g., social media platforms), to healthcare professionals (e.g., clinical grand rounds) and to relevant organizations (e.g., North American Menopause Society) will be completed. If results demonstrate the effectiveness of the CBT-SC-Peri protocol, and no adverse consequences that outweigh the benefits are observed, it is anticipated that the use of CBT-SC-Peri will be disseminated widely and implemented into menopausal care. Researchers on the study team (e.g., co-investigators) who have made significant contributions to the design, implementation, and analysis of study data, will be granted authorship for planned and unplanned publications. Further, a lay information package summarizing the study results will be constructed for any participant who expresses interest in receiving the results of the study.

## Discussion

Although cognitive and behavioral therapies for the treatment of menopausal symptoms have received empirical support, sexual concerns within this population are often neglected despite their high prevalence. To our knowledge, this study will be the first to investigate the efficacy of a cognitive-behavioral based treatment protocol aimed at improving sexual concerns experienced during perimenopause. While the intention of this treatment is to primarily target sexual concerns, we also anticipate improvements in vasomotor symptoms, anxiety, depression, and relationship satisfaction. If successful, this study will provide an evidence-based, non-pharmacological treatment for women experiencing untreated sexual concerns during perimenopause. Further, this study could provide the basis for a larger randomized controlled clinical trial to confirm the efficacy of this psychological intervention. As consumer demand increases for alternative treatments for these symptoms during perimenopause, this form of treatment may not only be preferred by some, but necessary for others as hormonal treatments, including controversial testosterone treatment, have adverse risks associated with them. Ultimately, this study has the potential to positively impact a significant proportion of the population, as 28.3% of the Canadian population is comprised of women between the ages of 45-64 years old (46). This study will also have a direct impact on healthcare service delivery by utilizing a manualized psychotherapy approach that would allow training of new health professionals, thereby increasing the treatment's availability to consumers.

## Ethics Statement

This study, involving human participants, was reviewed and approved by the Hamilton Integrated Research Ethics Board (HIREB). The patients/participants win this study have/will provide their written informed consent to participate in this study.

